#### Mediators of change

Potential mediators will be assessed at T1-T4 and at the intermediate measurement T1b/T2b: (1) parent/caregiver-reported positive and negative parenting practices (measured with the FPNE, see above), and (2) use of strategies to regulate affect and to reduce anger as reported by the patient and the parent/caregiver. Additionally, the child’s AD symptoms will also be assessed at the intermediate measurements using patient- and parent/caregiver-rated DADYS questionnaires (see above) to determine whether changes in the potential mediators preceded changes in outcome.

For the assessment of strategies to regulate affect and reduce anger, as reported by the patient and the parent/caregiver, we adapted the German questionnaire for the assessment of emotion regulation (FEEL-KJ) [96]. The questionnaire for patient rating was slightly modified and enhanced. The items were then reworded for parent/caregiver rating.

Strategies to regulate emotions of the child by the parent/caregiver will be assessed in parent/caregiver report with a modified version of the Coping with Children’s Negative Emotions Scale (CCNES; German Version VEEB) [97].

### Sample size

In total, *n* = 597 children will be recruited for ADOPT Online. The community sample will be drawn by ADOPT Epidemiology. A screening tool for AD in children and clinician’s rating in the outpatient sample will then be used to identify the AD and the No AD sample. At T1, inclusion and exclusion criteria will be evaluated for the AD sample, resulting in an estimated sample size of *n* = 497 children, who will be randomized with an allocation rate of 5 (ADOPT Online; *n* = 414) to 1 (TAU; *n* = 83).

In ADOPT Treatment, *n* = 232 children need to be recruited and randomized with an allocation rate of 1 (THOPAS; *n* = 116) to 1 (TAU; *n* = 116). T3 assessment needs to include *n* = 198 patients from the treatment and control group (232 patients minus 34 lost at T3, i.e., 20%). At T4, a total of *n* = 158 patients will be assessed for further follow-up (assuming a further dropout of 20% from T3).

As the study designs of ADOPT Online and ADOPT Treatment include a stepped care process, the sample size is defined by the expected effect sizes of the ADOPT Treatment step. The effect sizes found in the reported meta-analyses of trials on the effects of mostly standardized treatments in a group format (mostly compared with waiting list control) are in the range of *d* = 0.3 to 0.6. The effect sizes of personalized individual treatments tend to be elevated, in the range of 0.6 to 0.8 [51, 98]. The planned trial will be conducted with online treatment-refractory AD and may therefore comprise a more severe group of patients, who may be harder to treat. Thus, a moderate effect size of *d* = 0.5 is expected. The two-sample *t*-test with an allocation ratio of 1:1 (THOPAS: TAU) requires 64 patients per group in order to attain a power of 80% at a two-sided significance level of 5%. A similar therapist effect (due to clustering) as in [99] yields a design effect of 1.4 (intraclass correlation 0.1, five patients per therapist on average); thus, *n* = 179 [128*1.4] patients are required [100]. Further accounting for heterogeneous cluster sizes (+ 10%) and attrition (+ 15%) yields approximately *n* = 232 patients to be randomized (*n* = 116 to THOPAS, *n* = 116 to TAU). Note that power is further increased by taking a baseline-adjusted analysis of covariance (ANCOVA)/mixed model for repeated measures (MMRM) approach for statistical analysis. We expect a male:female ratio of 7:3 [51]. Thus, the sample size of ADOPT Treatment is set at *n* = 232, with *n* = 116 in the treatment arm and *n* = 116 in the control group.

Meta-analyses of self-help PMT report effect sizes between 0.61 and 1.01 [25, 27], with smaller effects for self-help interventions with no therapist contact. It remains unclear whether symptom severity serves as a moderator favoring severely affected children in PMT [22]. Breitenstein [27] reported mean completion rates of about 78% in their meta-analysis on online PMT. In studies on self-help PMT, dropout ranged between 5 and 30% [28, 56]. On the other hand, for highly burdened parents, like those in our AD sample, online interventions might be harder to successfully complete. Given this, and the fact that online PMT without therapist contact is already less effective than telephone-assisted self-help interventions, a small effect size such as 0.378 should be expected for ADOPT Online. Thus, the two-sample t-test with an allocation ratio of 5:1 (ADOPT Online: TAU) requires 331 and 66 patients, respectively, to attain a power of 80% at a two-sided significance level of 5%. Further accounting for 20% attrition yields about *n* = 497 [≈ 397/0.8] patients to be randomized (*n* = 414 to ADOPT Online, *n* = 83 to TAU). Note that power is further increased by taking a baseline-adjusted ANCOVA/MMRM approach for statistical analysis. We expect a male:female ratio of 7:3 [51]. Missing data and non-compliance will be dealt with by performing intention-to-treat (ITT) analysis.

In ADOPT Institution, a screening tool for AD in children will then identify the AD (*n* = 166) and the No AD (*n* = 80) sample in a total of *n* = 750 children in OHC. According to the cut-off developed in ADOPT Epidemiology, we expect that at least 25% of the screening sample will be identified as screening-positive. Since the institutions have already agreed to take part in the project, we expect that most of the children screened positive will participate in the intervention. A total of *n* = 166 children need to be recruited and randomized with an allocation rate of 1 (THOPAS) to 1 (TAU) (83 to the experimental treatment, 83 to TAU). T2 assessment needs to be conducted with *n* = 140 patients from the treatment and control group (166 patients minus 26 lost at T2, i.e., 20%) and 64 from the No AD group. At T4, a total of 169 patients will be assessed for further follow-up (assuming a further dropout of 20% from T2).

The planned trial will be conducted with children in OHC, who presumably have a higher comorbidity load and may therefore constitute a more severe group of patients, who may be harder to treat. Thus, a moderate effect size of *d* = 0.6 is expected. The two-sample t-test with an allocation ratio of 1:1 (THOPAS:TAU) requires 45 patients per group to attain a power of 80% at a two-sided significance level of 5%. A similar therapist effect (due to clustering) as in [99] yields a design effect of 1.4 (intraclass correlation 0.1, five patients per therapist on average); thus, *n* = 126 [≈(45 + 45)*1.4] patients are required. Further accounting for heterogeneous cluster sizes (+ 10%) and attrition (+ 15%) yields about *n* = 166 [≈126/0.9/0.85] patients to be randomized (*n* = 83 to THOPAS, *n* = 83 to TAU). Based on previous experience, we expect that 664 patients need to be screened for eligibility (i.e. only 25% are eligible). Note that power is further increased by taking a baseline-adjusted ANCOVA/ MMRM approach for statistical analysis. We expect a male:female ratio of 7:3 [39].

### Data management and confidentiality

ADOPT Coordination, in cooperation with the Clinical Trials Center Cologne (CTCC), will provide electronic questionnaires within the framework of a remote data entry system (REDCap) [101] and will administer the database. REDCap is a proprietary remote data entry system which was developed by Vanderbilt University, Nashville, TE, USA. An instance of REDCap is hosted and maintained by the CTCC. Each investigator/data entry personnel will receive separate access information for the use of the REDCap system. An audit trail within REDCap provides a data history of which data were entered, changed or deleted, when and by whom. The data will be reviewed for completeness, consistency and plausibility. Data corrections will be entered directly into REDCap by the responsible investigator or a designated person.

Details of the data management (procedures, responsibilities, timelines, data validation and data corrections) will be described in a data management manual (DMM) prior to trial start. The DMM is a working document that is adapted during the clinical trial and contains a record of all data management processes carried out.

Each patient will receive a consecutive patient identification number (ID) after screening. The ID will be entered in the centralized database (REDCap) for the registration of the patient.

For ADOPT Institution, the ID will be assigned by the person who completes the screening questionnaire (i.e., the caregiver) with instructions provided by ADOPT Institution. Thus, screening can be performed without disclosure of identifying information of the child in the study center. After identification of a screening-positive case and after informed consent of the guardians has been obtained, the child and caregiver will be invited for T1 assessment and further participation in ADOPT Institution.

ADOPT Coordination, in cooperation with the CTCC and the PIs, will process data through personnel who are specifically trained for the study, and who will then work in accordance with the standard operating procedures (SOPs) of the study centers. Legal regulations for data protection will be fulfilled.

### Statistical analysis

#### Patient demographics/other baseline characteristics

Demographic and other baseline data (including disease characteristics) will be obtained at T1 and will be summarized descriptively using all documented patients.

Continuous data will be summarized by arithmetic mean, standard deviation, minimum, 25% quantile, median, 75% quantile, maximum, and the number of complete and missing observations. If appropriate, continuous variables can also be presented in categories.

Categorical data will be summarized by the total number of patients in each category and the number of missing values. Relative frequencies will be displayed as valid % (number of patients divided by the number of patients with non-missing values).

#### Analysis of primary endpoint

The primary (full) analysis set is derived from the ITT principle (all patients randomized with a valid baseline assessment: ADOPT Online/ADOPT Institution: T1/ADOPT Treatment: T2 and at least one follow-up measurement). The primary outcome measures “change in AD symptoms from T1 to 13 weeks post-randomization (T2)” (ADOPT Online), “change in AD symptoms from T2 to 32 weeks post-randomization (T3)” (ADOPT Treatment) and “change in AD symptoms from T1 to 32 weeks post-randomization (T2)” (ADOPT Institution) will be evaluated by an ANCOVA, with fixed effects baseline, study center, gender and treatment arm and corresponding marginal means and contrast tests (type II sums of squares). Interactions of study center and gender with treatment arm will be explored. Data from study centers with low recruitment (i.e., < 10 patients) will be pooled. The potential clustering of observations of participants by therapist or center will be investigated using multilevel modelling. Multiple imputation approaches will be taken to assess the robustness of the results. Specifically, missing values will be separately imputed by type assuming mixtures of missingness-not-at-random patterns [102]. Imputation data sets will be post-processed by multiplication with factors and addition of offsets (tipping point analysis) [103]. Proxy measures will be taken into account to ameliorate the effects of attrition.

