#### Missing values

It should be emphasized that as few patients as possible should discontinue treatment and that all patients should be followed up and also documented after discontinuation of the treatment in order to record data required according to the ITT principle. To assess the impact of up to 20% attrition, multiple imputation approaches will be taken, accounting for proxy measures and assuming specific missingness-not-at-random patterns. The details will be documented in a statistical analysis plan. Analysis of subjects essentially observed and treated per protocol is supportive.

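### The primary set, described as ITT-derived, requires a follow-up measurement, so as written the imputation and tipping-point analyses cannot cover children who have baseline data only

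*Protocol article*

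**What the plan says.** The section *Analysis of primary endpoint* states: "The primary (full) analysis set is derived from the ITT principle". It then defines that set as "all patients randomized with a valid baseline assessment: ADOPT Online/ADOPT Institution: T1/ADOPT Treatment: T2 and at least one follow-up measurement". An ANCOVA of change to T2 (Online, Institution) or T3 (Treatment) is the primary analysis.

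On missing data the same paragraph says: "Multiple imputation approaches will be taken to assess the robustness of the results". It adds a tipping-point step that rescales and shifts the imputed values. Neither analysis is given a set of its own.

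The section *Missing values* gives the purpose: "To assess the impact of up to 20% attrition, multiple imputation approaches will be taken". On follow-up it asks the following: "all patients should be followed up and also documented after discontinuation of the treatment in order to record data required according to the ITT principle". For ADOPT Online, the section *Sample size* says: "Missing data and non-compliance will be dealt with by performing intention-to-treat (ITT) analysis".

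**The concern.** Having a follow-up measurement is an event after randomisation. A set that depends on it is not the randomised set, and it leaves out the children about whom least is known. Imputation and tipping-point analyses show how far the result depends on what happened to missing children, and they can do so only for children who are in the data set. If children with baseline data only are removed first, the announced assessment of attrition covers only part of the attrition, possibly none of it in ADOPT Online.

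The article itself expects missingness to be informative: it plans missing-not-at-random patterns. A reassuring tipping-point result from a reduced set could be read as evidence that the result survives 20% attrition when most of that attrition was never tested.

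**Working it through.** **1. The plan's own attrition figures.**
- Online (*Sample size*): d = 0.378, ratio 5:1, two-sided 5%, power 80%. By the normal approximation the control arm needs (1 + 1/5) × (1.960 + 0.842)² / 0.378² ≈ 66, and the active arm 5 × 66 = 330. The t-test gives 66.2 and 331.2, matching the stated 66 and 331 (total 397). Then 397/0.8 = 496.25, rounded up to the stated 497. Expected loss: 497 − 397 = 100 (20%).
- Treatment: 232 − 198 = 34 lost at T3 (34/232 = 14.7%, although the text labels it 20%).
- Institution: 166 − 140 = 26 lost at T2 (26/166 = 15.7%, also labelled 20%).

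**2. Which lost children can meet the follow-up rule** (*Participant timeline*, *Trial design*, *Mediators of change*).
- Online: no outcome assessment is scheduled between T1 and the T2 endpoint. A child lost before T2 qualifies only by returning at T3 or T4. Four visits are planned for all Online patients. However, *Trial design* sorts children for T3 and T4 by their T2 status and describes no route for a child without a T2 rating.
- Treatment and Institution: T2b and T1b come before the endpoint and include parent- and child-report AD questionnaires, but no clinical interview. A child lost after T2b or T1b qualifies if a questionnaire counts as follow-up. If only the blinded interview counts, that child does not qualify on T2b or T1b. The article does not define the term.

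**3. Effect on the set.** Let f be the share of lost children with no qualifying follow-up. The article does not give f, so its range is 0 to 1.

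| Trial | f = 1: set / left to impute | f = 0.5 | f = 0 |
|---|---|---|---|
| Online | 397 / 0 | 447 / 50 | 497 / 100 |
| Treatment | 198 / 0 | 215 / 17 | 232 / 34 |
| Institution | 140 / 0 | 153 / 13 | 166 / 26 |

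**4. Effect on the tipping point (Online, illustration).** Assume an estimate of 0.378 SD, a standard error fixed at its value for 331 and 66 children, and an offset applied only to missing active-arm children.
- Standard error = √(1/66 + 1/331) = 0.135. Critical d = 1.96 × 0.1348 = 0.264.
- Room before significance is lost: 0.378 − 0.264 = 0.114 SD.
- Offset needed = 0.1138 / share imputed. All 20% imputed: 0.1138/0.20 = 0.57 SD. Half: 0.1138/0.10 = 1.14 SD. A quarter: 0.1138/0.05 = 2.28 SD. None: no offset can change the result.
- These shares are fractions of all randomised children. On the smaller set, the half case is 50/447 = 11.2%, and the offset is 0.1138/0.112 = 1.02 SD. The direction is the same.

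**The case against.** The strongest reply has three parts.

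First, the article leaves the details of missing data and attrition to a statistical analysis plan that is not shown, and it never says that imputation excludes children with baseline data only. Its stated purpose even suggests that they are meant to be covered. This stands as a limit: confinement to the set is the natural reading of the paragraph, not an explicit statement. The set rule itself, however, is fixed in the article and not deferred, and as worded it works against that purpose.

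Second, a reader might infer that nearly every child lost before the endpoint leaves the set in all three trials, and that only intermittent gaps remain to be imputed. The documents do not support that. The rule asks for any follow-up measurement, so the T2b and T1b questionnaires can satisfy it, and a later Online visit can too. The counts of 34 and 26 are therefore upper limits, and so is the 100 in Online.

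Third, a reader might infer that the clause turns the primary result into a completer comparison. It does not: an ANCOVA on observed change omits children without the endpoint under any set definition. Nor does the article support a fixed bias, such as 0.378 against 0.8 × 0.378 = 0.30 SD. That figure needs every Online dropout to gain nothing and 0.378 to be a completer effect, yet the article chose 0.378 partly because burdened parents may not finish the programme. Not using the online tool, or leaving therapy, is also not loss to follow-up, since such children are to be followed up and, once assessed, are in the set.

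**Conclusion.** The point holds for the analysis set and the robustness analyses. A set presented as ITT carries a condition set after randomisation, and no wider set is named for the analyses meant to assess attrition. ADOPT Online is the most exposed, because it has no assessment before its endpoint visit. ADOPT Treatment and ADOPT Institution are partly affected, or fully if only the blinded interview counts as follow-up.

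The harm is that sensitivity analyses would overstate robustness. How much depends on the timing of dropout and on how many children return, neither of which the article gives. The size of any bias in the primary estimate cannot be derived from the article.

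**What to change.** - In *Analysis of primary endpoint*, delete the requirement of at least one follow-up measurement. Define the full analysis set as all randomised children with a valid baseline, analysed as randomised.
- State that the planned multiple-imputation and tipping-point analyses run on that set and include children with baseline data only.
- Label the ANCOVA on observed endpoints as an observed-case analysis.
- In *Sample size*, narrow the Online sentence instead of deleting it: ITT addresses non-compliance, and the imputation analyses address missing data.

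Cost: a wording change, plus extension of imputation work that is already planned. Sensitivity intervals may be slightly wider and results less favourable. No additional recruitment is needed, because the randomised numbers already allow for attrition.

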ADOPT Online, ADOPT Treatment and ADOPT Institution are all part of the research consortium ADOPT (Affective Dysregulation – Optimizing Prevention and Treatment; https://www.adopt-studie.de). The goals of the umbrella project are to (a) investigate the epidemiology of AD including prevalence of symptoms and disorders, and biological and psychosocial risk and protective factors (ADOPT Epidemiology; ADOPT Neurobiology); (b) develop and evaluate screening and assessment tools (ADOPT Epidemiology; ADOPT Treatment); and (c) develop and evaluate treatment approaches for clinically useful personalized medicine in two cohorts of children with AD (ADOPT Online; ADOPT Treatment; ADOPT Institution; see detailed description below).

The primary objective of ADOPT Online is to assess the overall efficacy of a PMT program that can be accessed over the Internet (Online Parent Self-Help of Affective Dysregulation and coexisting disorders; ADOPT Online). In general, self-help or online PMT have proven to be effective in reducing child behavior problems. However, they might only be capable of reaching a subpopulation of parents [56], e.g., those who are better educated, less burdened, or whose children are less affected. Self-help interventions can thus serve as a time- and cost-effective first step of intervention that can reduce symptoms in a subpopulation [25, 49].

In the framework of a stepped care approach, the primary objective of ADOPT Treatment is to assess the overall efficacy of a personalized modular outpatient treatment of AD and coexisting disorders (Therapy for Optimizing Affective Regulation in children; THOPAS) in children with substantial residual symptoms of AD after parents have received Internet-based PMT (in ADOPT Online).

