### Allocation

Patients fulfilling the eligibility criteria at T1 will be centrally registered and will be randomly assigned to the treatment groups (ADOPT Online or TAU, allocation ratio 5:1; THOPAS or TAU, allocation ratio 1:1) according to permuted blocks of varying length. Randomization will be stratified by recruitment process (ADOPT Online and ADOPT Treatment), gender and study site (i.e. 20 strata altogether for ADOPT Online/ADOPT Treatment, 12 strata altogether for ADOPT Institution) and implemented as a central 24–7 Internet service (ALEA, FormsVision BV, Abcoude, NL) operated by local authorized study staff. Treatment assignments will be displayed on screen and delivered by e-mail. The randomization service will be maintained by the IMSB, University of Cologne.

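### ADOPT Online randomizes 5:1 but is tested with a common-variance ANCOVA; if self-help works only in a subgroup, the test is conservative and loses power that a robust standard error would keep

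*Protocol article*

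**What the plan says.** - **Primary model.** Under Analysis of primary endpoint, the change in the AD symptom score "will be evaluated by an ANCOVA, with fixed effects baseline, study center, gender and treatment arm", with "corresponding marginal means and contrast tests (type II sums of squares". One specification covers ADOPT Online, ADOPT Treatment and ADOPT Institution.
- **Allocation.** The Allocation section gives "ADOPT Online or TAU, allocation ratio 5:1"; both THOPAS trials use 1:1.
- **Sample size, ADOPT Online.** The Sample size section states that "a small effect size such as 0.378 should be expected for ADOPT Online". It derives 331 and 66 patients for 80% power at a two-sided 5% level. "Further accounting for 20% attrition yields about" 497 randomized (414 and 83).
- **Expected pattern of effect.** The Background says of self-help and online programs that "they might only be capable of reaching a subpopulation of parents", and calls them a "time- and cost-effective first step of intervention that can reduce symptoms in a subpopulation".
- **Related provisions.** Multilevel modelling is planned for clustering by therapist or center, and multiple imputation for missing data. The heterogeneous covariance under Analysis of secondary endpoints is heterogeneous over time, not by arm. None of these deals with different variances in the two arms.

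**The concern.** An F or t contrast from type II sums of squares divides the arm difference by a standard error built on one residual variance. With equal arms, unequal variances cancel out of that standard error. With 331 against 66 they do not. The pooled variance is about 84% Online (330 of 395 degrees of freedom), while about 83% of the sampling variance of the contrast comes from TAU when the variances are equal (0.01515 of 0.01817, see the working).

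The article itself gives a reason why the variances might differ. If some Online families gain a lot and the rest nothing, outcomes spread out in the Online arm only. At stake are the width of the confidence interval and the power of the ADOPT Online primary test. The point estimate is not affected.

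**Working it through.** **Inputs.** From the article: 331 Online and 66 TAU evaluable, d = 0.378, two-sided 5%, 80% power, five centers, male:female 7:3. Assumed, because the article does not give them: the ratio r = Var(Online)/Var(TAU), the responder share p, and a baseline correlation of 0.5 for the ANCOVA simulation.

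**1. The article's own figure.** n(TAU) = (1.960 + 0.842)² × (1 + 1/5) / 0.378² = 7.849 × 1.2 / 0.1429 = 65.9, so 66 TAU and 330 Online; the article has 331. Power at 331/66 is 80.1% by the normal approximation. Attrition: 397/0.8 = 496.25, so 497. The figure is reproduced.

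**2. Pooled against true standard error.** With Var(TAU) = 1:
- pooled SE² = [(330r + 65)/395] × (1/331 + 1/66)
- true SE² = r/331 + 1/66
- f = pooled SE / true SE; the test behaves as if its critical value were 1.96f.

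At r = 1 both SE² are 0.00302 + 0.01515 = 0.01817, so f = 1. In a 1:1 trial f = 1 for every r, which is why the other two trials are essentially unaffected.

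**3. The subgroup idea in numbers.** Let a share p of Online families gain 0.378/p and the rest nothing, so the mean effect stays 0.378. Then r = 1 + 0.378² × (1 − p)/p.

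Worked case, p = 0.3: r = 1 + 0.1429 × 2.333 = 1.333. Pooled SE = √(1.2785 × 0.01817) = 0.1524. True SE = √(1.333/331 + 1/66) = 0.1385. f = 1.10. Pooled power = Φ(0.378/0.1385 − 1.96 × 1.10) = Φ(0.57) = 71.6%. With the correct SE it is Φ(0.77) = 77.9%.

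| Responder share | r | f | Power, pooled | Power, correct SE |
|---|---|---|---|---|
| all equal | 1.00 | 1.00 | 80.1% | 80.1% |
| 80% | 1.04 | 1.01 | 79.2% | 79.8% |
| 50% | 1.14 | 1.05 | 76.5% | 79.1% |
| 30% | 1.33 | 1.10 | 71.6% | 77.9% |
| 20% | 1.57 | 1.16 | 65.7% | 76.4% |

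These are unadjusted figures, on the same basis as the article's 80%.

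**4. The stated ANCOVA, simulated.** Baseline, five centers, gender and arm; 331/66; 4,000 trials per row.

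| Responder share | Power, pooled | Power, HC3 | Difference, HC3 minus pooled |
|---|---|---|---|
| all equal | 89.2% | 88.5% | −0.7 |
| 50% | 86.0% | 87.8% | +1.8 |
| 30% | 80.5% | 85.7% | +5.2 |
| 20% | 74.6% | 85.0% | +10.3 |

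A repeat with 20,000 trials per row gave differences of −0.6, +1.9, +5.2 and +9.7.

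**5. Calibration with no mean effect.** In 6,000 simulated trials per value, r = 0.5, 0.75, 1, 1.25, 1.5 and 2 gave pooled rejection rates of 11.8%, 7.5%, 4.9%, 3.5%, 2.7% and 1.5%; HC3 stayed between 4.5% and 5.1%. In SD terms, a TAU/Online ratio of 0.8 gives about 2.3% and a ratio of 1.2 about 8%.

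**The case against.** **The estimator belongs in the SAP.** The article names no residual-variance assumption, it leaves details to an SAP that is not shown, and that SAP may already specify a robust estimator. So the absence of one from the article is not an error. But the point does not rest on silence. The article names sums-of-squares contrast tests, whose ordinary form has one residual variance, and carries them unchanged from the 1:1 trials to the 5:1 trial. Common variance remains a fair inference from that wording, not a declared choice.

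**The subgroup rationale is tentative.** The Background says self-help might reach only a subpopulation, and says so to justify stepped care. It gives no share, and the Sample size section plans on one mean effect. The all-or-nothing mixture is an assumption of this check. This stands, and it is why the size is a range.

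**The loss is modest.** With baseline adjustment, which the article itself says adds power, the pooled ANCOVA still reaches about 80% or more at responder shares of 30% and above. This also stands.

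**A stronger reading fails.** A reader might infer that the primary test has an inflated false-positive rate. That would need TAU to be the more variable arm. One could argue that TAU allows varied care while other intensive therapy is not permitted in the experimental conditions (Concomitant care). But current or planned intensive behavioral therapy excludes a child from either arm of ADOPT Online, and the article nowhere reports or suggests a larger TAU variance. The subgroup rationale points the other way. If the program helps nobody, that mechanism creates no variance difference and the 5% level holds.

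**Conclusion.** The point holds as a matter of efficiency and protection, not as an error that would make a positive result untrustworthy. At 5:1 the common-variance contrast is not protected against unequal arm variances, and the one pattern the article mentions would make it conservative. Compared with HC3, the ADOPT Online ANCOVA then loses about 2 power points at 50% responders, 5 to 6 at 30% and about 10 at 20%. At 80% responders the loss is negligible.

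These figures rest on 331/66 evaluable children, a mean effect of 0.378, a baseline correlation of 0.5 and an all-or-nothing effect. The last two are not in the article, which gives no SDs or responder share. Type I error of about 8% at a TAU/Online SD ratio of 1.2 shows how sensitive the test is. It is not a prediction for this trial.

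**What to change.** For ADOPT Online, keep the ANCOVA and its point estimate, but state that the primary test and confidence interval use HC3 standard errors, or arm-specific residual variances with Satterthwaite degrees of freedom. Give the 5:1 allocation as the reason. If the SAP already says this, nothing more is needed; otherwise add the sentence before treatment codes are linked to outcomes.

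The cost is one sentence. If the arm variances turn out equal, the simulated loss of power is 0.6 to 0.7 points. The estimand and sample size stay as they are. ADOPT Treatment and ADOPT Institution need no change on this account.
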